# Study Treatment:

(a) Dosing schedule (dose, frequency, and duration):

Participants will be dispensed IP, which is Cap IP or Cap. Placebo.

Dose of the IP is: For 15 days two Capsules two times a day, and from 16^th^ day one capsule two times a day upto day 30. It is to be administered orally with plain water.

IP, in any dose, needs to be taken for a period of 30 days in total; from the day of enrollment.

IP will be given from the study site by the study coordinator, free of cost. All other concomitant medicines prescribed by the treating physician/doctor has to be taken by the patient.

Half of the patients enrolled will get Placebo (inert substance) in the capsule throughout the study period. However, neither patient nor the investigators will know, who is receiving what.

(b) Study drug supplies and administration: Study medication will be provided by AMAI Charitable Trust, Pune, which is the sponsor of the trial. Quest clinical services will distribute the same to the enrolled patients in the manner mentioned in this protocol. Investigational drug formulation has been manufactured following all the GMP regulations.

The IP will be securely stored in cupboards; at room temperature. Expiry date will be verified before giving the IP to the patients. CRC will document the code on the bottle to given to corresponding patient.

(c) Dose modification for study drug: In case of any serious adverse event, that warrants to break the blind, sponsor will be contacted. Dose might be modified or IP might be stopped, in the best safety interest of the patient.

(d) Possible drug interactions: As this is an herbo-mineral compound, involving safe profile herbs, no drug interactions are expected. Investigator already has an experience with the combination. When he has used it for other infectious and non-infectious disorders for immunity boosting.

(e) Concomitant therapy: As a part of the study design, all the medicines that the patient is supposed to take for his/her other condition(s), patient might be having, will be allowed. There is no drug that is not allowed, provided, it is prescribed by the treating physician. If the PI or co-PI decides that by remaining in the study could be harmful for his/her health, patient will be discontinued from the study.

(f) Blinding procedures:

Placebo is used in this study, to allow blinding of investigators and subjects to treatment and minimize bias in the evaluation of safety and efficacy assessments,

Subjects, investigator staff and personnel performing the study assessments will remain blinded to the identity of the treatment from the time of randomization. Monitoring will be done by unblinded personnel from sponsor.

Following measures will be applied to keep required personnel blinded.

1. Sponsor will provide coded bottles containing IP or placebo in those.
2. The list of which bottle contains what will not be shared with any site member or with the CRO.

Adverse Events:

Very serious [allergic reaction](http://www.webmd.com/allergies/anaphylaxis-15/slideshow-allergy-triggers) to this drug should be rare. However, patient will be asked to seek immediate medical attention if he/she notices any symptoms of a serious allergic reaction, including: [rash](http://www.webmd.com/skin-problems-and-treatments/guide/common-rashes), [itching](http://www.webmd.com/skin-problems-and-treatments/guide/skin-conditions-pruritus)/swelling, severe [dizziness](http://www.webmd.com/first-aid/understanding-dizziness-basics), [trouble breathing](http://www.webmd.com/lung/breathing-problems-causes-tests-treatments).

Of particular interest, these drugs are generally regarded as safe.

Reporting of the adverse events will be done in following format:

1. Patient Details:

Initials and other relevant identifier (PID)*

Gender:

Age:

Weight:

Height:

1. Suspected Drug(s)

Generic name of the drug(s)*

Indication(s) for which suspect drug was prescribed or tested

Dosage form and strength

Daily Dose and Regimen

Route of administration

Starting date and time of day

Stopping date and time of day or duration of treatment

1. Other Treatment(s)

The same information for concomitant drugs (including non-prescription/OTC drugs) and non-drug therapies, as for the suspected drug(s) will be provided.

1. Details of Suspected Adverse Drug Reaction(s)

Full description of reaction(s) including body site and severity, as well as the criterion (or criteria) for regarding the report as serious will be provided. In addition to a description of the reported signs and symptoms, whenever possible, a specific diagnosis for the reaction will be described.*

Start date (and time) of onset of reaction

Stop date (and time) or duration of reaction

De-challenge and re-challenge information

Setting (e.g., hospital, out-patient clinic, home, nursing home)

1. Outcome

Primary Outcome:

- Efficacy of the herbal extracts in COVID 19 positive patients (in declining viral load: time-point: 5 days and early recovery)

Secondary Outcomes:

- - Efficacy of the herbal extracts as an immune-modulator - TH1, TH2, Th17, IL6, NK Cells and CD markers; Immunoglobulin IGG (Serum); Immunoglobulin IGM (Serum): at 30 days.
  - Efficacy of the investigational product in reducing sequela of the disease
  - Safety analysis (Liver Function Test and Kidney Function Test) including serious allergic reaction of: rash, itching/swelling, severe dizziness, trouble breathing.

1. Details about the Investigator*

Name

Address

Telephone number

Profession (specialty)

Date of reporting the event to Ethics Committee:

Signature of the Investigator

Information marked ‘*’ must be provided.

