# Study Design

Overview of the Study Design

- This is a randomized, 2-arm, parallel group, double-blind, 1:1 ratio, controlled, exploratory trial with a study period of 30 days from the of enrolment.
- A total of up-to 75 known COVID-19 positive (with positive RT-PCR) patients will be enrolled in the study.
- All the patients enrolled in the study will get the Investigational Product (IP-1 and IP-2), or 2 capsule of Placebo in similar sized and colored bottles, two times daily for the 1^st^ 15 days. From 16^th^ day onwards patients will get one capsule twice daily i.e. IP-2 or capsule placebo up to day 30.
- Patients will undergo laboratory investigations upon enrolment and on last visit. RTPCR for COVID will be done on day 5 (+ 1 day).
- Patients and doctors treating will not be knowing what the participating subject has received. Subjects will be given coded bottles, containing dose for 30 days.
- No medicine which his/her physician is giving will be stopped. No modifications shall be suggested in their diet and daily routine physical activities.
- Thus, patients enrolled in the study will get the IP / Placebo in addition to the standard of care which they were already receiving at the time of enrolment.
- Half of patients will be getting Cap. IP and half will be getting Cap. Placebo throughout the study duration of 1 month.

Study period for enrolled patients will be 30 days:

- Enrollment (day 0): After Informed Consent Process, Demographics and other information for CRF will be recorded. Investigations: COVID 19 RTPCR, Lymphocyte subset analysis (TH1, TH2, Th17, IL6, NK Cells and CD markers); Immunoglobulin IGG (Serum); Immunoglobulin IGM (Serum); Liver Function Test and Kidney Function Test will be done. Cap. bottle will be given to the patients with the dose lasting for 30 days.
- Day 3±1: COVID-19 RT PCR (quantitative) test will also be conducted on day 3 (±1) on 5 subjects of each group
- Follow-up 1: Day (5±1): COVID-19 RT PCR (quantitative) test will be conducted for all subjects on Day (5±1). CRF will be filled for knowing the overall status.
- Follow up 2 (15^th^ day+ 2 days): This follow up will be clinical/telephonic. CRF will be filled for knowing the overall status.

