- Follow up 3 (30^th^ day+ 2 days): Patients will be followed up at day 30. This visit will be done telephonically. Patient will not visit site but blood investigations shall be carried out. Investigations will be done outside the site, considering that the site is COVID specific hospital. The investigations are; Lymphocyte subset analysis (TH1, TH2, Th17, IL6, NK Cells and CD markers); Immunoglobulin IGG (Serum); Immunoglobulin IGM (Serum); Liver Function Test and Kidney Function Test will be done. All the unused IP will be collected.
- Sponsor will provide 10 codes (5 from each, IP and placebo, not mentioning which is placebo and IP). These will get Sr. Ferritin, CRP and D- Dimer done for same patients on day 0.

Every time subject coming to the scheduled follow-up should be asked to bring the remaining capsules with the bottle.

Flow chart

Screening

(I/E Criteria, ICF reading)

Enrollment (Day 0) Randomization

IP Arm Placebo Arm (30 patients in each arm)

(Consenting, Clinical Exam, Investigations, QOL, IP / Placebo Dispense)

COVID-19 RT PCR (quantitative) test on day 3 (±1) for 5 subjects of each group

1^st^ Follow-up: Day (5±1)

COVID-19 RT PCR (quantitative)

2^nd^ Follow-Up: Day (15+2)

[Clinical/telephonic]

3^rd^ Follow-Up: Day (30+2)

[Tele follow-up Blood Investigations at lab]

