# Study Assessments:

Participants will have a minimum of two follow-ups. Clinical assessment will be done; vitals will be noted, questionnaire will be filled-in and blood will be collected for various parameters.

Study Conduct:

Patients screened, eligible and willing will be enrolled in the study and IP will be dispensed. During screening, inclusion-exclusion criteria will be applied. Those fulfilling the criteria will be given detailed information about the study. Of those who are willing to participate will be asked to sign the informed consent form. Study coordinator with the principal or co-principal investigator will participate in the consent process.

Day of consenting will be done on the day of screening. After signing the consent form, on enrollment day, physical examinations will be done; blood will be withdrawn for investigations, case record form will be filled and IP will be dispensed. A copy of duly signed informed consent form will be given to them.

Follow-up Visit 1 [5^th^ day (+ 1) of the day of enrollment]: Questions will be asked about adherence, missed doses if any and adverse events if any. NP swab will be collected for RT-PCR of COVID-19

Follow-up Visit 2 [15^th^ day (+ 2) of the day of enrollment]: All the procedures for this visit will be the same as that of Visit 1, except that swab will not be collected for RT PCR.

Follow-up Visit 3 [30^th^ day (+ 2) of the day of enrollment]: All the procedures for this visit will be the same as that of Visit 2, and in addition, blood will be drawn for various markers.

Discontinued Patients:

Patients will be withdrawn/dropped from the study if they violate the protocol e.g. by participating in other study, by not taking the IP, not coming to the hospital for follow-up etc. Patients developing any serious disease, patients wanting to withdraw will also be withdrawn from the study.

Patients who have not turned for clinical follow-up will be called telephonically up to three times after the window period is over. During consenting they will be asked if it is alright with them.

However, as it is a ‘intent-to-treat’ (ITT) study design, data collected of such patients, till they are dropped out/withdrawn from the study will be included in the analysis.

Patients will be insisted to visit during the window-period. Those who miss this will still be continued into the study. On case-to-case basis, protocol waivers will be granted by the co-PI and/or the PI.

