# Study Assessment Table

| Visit🡪 | Screening | Visit  Enrolment | 1^st^ Follow up | 2^nd^ Follow up | 3^rd^ Follow up |
| --- | --- | --- | --- | --- | --- |
| Study Procedure | (Day -2 to Day 0) | Day 0 | Day 5^th^ (+1) | Day 15^th^ (+2) | Day 30^th^ (+2) |
| ICF | X | X |  |  |  |
| I/E Criteria | X | X |  |  |  |
| Demographics | X |  |  |  |  |
| Vitals and Physical Examination |  | X | X | X | X |
| Medical History | X |  |  |  |  |
| Questionnaire |  | X | X | X | X |
| Investigations |  | X*^#^ | X^#^ |  | X* |
| Bottle Dispensing |  | X |  | X |  |
| IP / Placebo Accountability |  |  | X | X | X |
| AE/SAE | X | X | X | X | X |

Investigations –

*TH1, TH2, Th17, IL6, NK Cells and CD markers; Immunoglobulin IGG (Serum); Immunoglobulin IGM (Serum); Liver Function Test and Kidney Function Test

Around 2 ml of blood will be stored for additional biomarker in Immunology and Virology.

^#^COVID-19 RT PCR (quantitative): This test will be conducted on day 3±1 day on 5 subjects of each group. Same group: Sr. Ferritin, CRP and D-Dimer will be done on day 0 and 5.

Clinical investigations like chest X ray, ECG will be done as per physician’s discretion. Vitals and Physical Examination: If physician is not in a position to perform, s/he will extrapolate the data from the available information.

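### Patients who leave before day 30 have no protocol-scheduled post-baseline liver or kidney result, so the laboratory safety comparison loses them, possibly for reasons related to harm

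*Protocol*

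**What the plan says.** **The outcome.** The list of secondary outcomes, placed after the adverse-event format in the Study Treatment section, includes "Safety analysis (Liver Function Test and Kidney Function Test) including serious allergic reaction of" rash, itching or swelling, severe dizziness and trouble breathing. It gives no time point for the laboratory part.

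**When the tests are done.** The Study Design overview says "Patients will undergo laboratory investigations upon enrolment and on last visit". The visit list in the same section puts the panel at enrolment and again at Follow-up 3, day 30 (+2): "Liver Function Test and Kidney Function Test will be done. All the unused IP will be collected". Study Assessments says of Visit 3: "All the procedures for this visit will be the same as that of Visit 2, and in addition, blood will be drawn for various markers". In the Study Assessment Table, the asterisked panel ("TH1, TH2, Th17, IL6, NK Cells and CD markers; Immunoglobulin IGG (Serum); Immunoglobulin IGM (Serum); Liver Function Test and Kidney Function Test") is marked at day 0 and day 30 only.

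**How patients leave early.** Study Assessments, on discontinued patients, says: "Patients will be withdrawn/dropped from the study if they violate the protocol e.g. by participating in other study, by not taking the IP", or by failing to attend. It adds: "Patients developing any serious disease, patients wanting to withdraw will also be withdrawn from the study". Study Treatment (e) says that if the PI or co-PI decides that "by remaining in the study could be harmful for his/her health, patient will be discontinued from the study". Study Assessments keeps in the analysis what was collected from such patients up to the point of withdrawal.

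**The concern.** Two of the exit rules, serious disease and an investigator's judgement that staying could be harmful, select the patients who matter most for safety. If they leave before day 30, the schedule provides only their day-0 liver and kidney values, which say nothing about change on treatment. The intent-to-treat wording in Study Assessments and Data Analysis does not help, because it covers data that were collected and here none were scheduled.

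The stake is the laboratory part of the safety outcome. Scheduled post-baseline values come only from patients who reach day 30. If leaving is linked to unrecognised liver or kidney change, abnormality is under-counted. If that link or the leaving rate differs by arm, the comparison between arms is biased as well. An analysis plan can describe the missing values but cannot recover samples that were never drawn.

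**Working it through.** **1. Schedule against exit rules.**

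| Point in study | Liver and kidney tests scheduled? | Source (Protocol) |
| --- | --- | --- |
| Day 0 | Yes | Study Design; Study Assessment Table |
| Day 3 (5 per group) | No; RT-PCR only | Study Design |
| Day 5 | No; RT-PCR, plus ferritin, CRP and D-dimer in the same 10 patients | Study Assessment Table |
| Day 15 | No investigations | Study Assessments; Study Assessment Table |
| Day 30 | Yes | Study Design; Study Assessments; Study Assessment Table |
| Exit for violation, serious disease or own wish | None written | Study Assessments |
| Exit because staying is judged harmful | None written | Study Treatment (e) |
| Non-attendance | Up to three telephone calls; no sample | Study Assessments |

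No early-termination visit is described. A patient who leaves between day 0 and day 30 therefore has no scheduled post-baseline value.

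**2. The plan's sample size.** Inputs: 5% against 35%, two-sided 5% level, 80% power, 1:1; mean proportion 0.20, difference 0.30.
- Kelsey: 2 × 0.20 × 0.80 × (1.960 + 0.842)² / 0.30² = 27.9, so 28 per arm and 56 in total, as stated.
- Fleiss without continuity correction: 27 per arm and 54 in total, as stated.

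The sample size is not in dispute. It serves only to find the recruitment margin.

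**3. Recruitment margin.** The protocol gives no drop-out rate. It says that, allowing for drop-outs, more than 60 and up to 75 subjects will be considered; Methods and Procedures also gives 60 as the total.
- Over 56: 60 − 56 = 4 (6.7% of 60); 75 − 56 = 19 (25.3% of 75).
- Over 54: 60 − 54 = 6 (10%); 75 − 54 = 21 (28%).

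These figures show how many losses recruitment could absorb. They do not predict how many patients will leave.

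**4. Illustration of the mechanism (assumed values, not in the Protocol).** Take 37 patients in one arm, a true rate r = 10% of liver or kidney abnormality, no other loss, and a fraction f of affected patients who leave before day 30 without the change being recognised. Expected cases are 37 × 0.10 = 3.7. The rate among those sampled at day 30 is r(1 − f) / (1 − rf).

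| f | Cases measured | Rate at day 30 |
| --- | --- | --- |
| 0 | 3.7 | 10% |
| 25% | 2.8 | 0.075 / 0.975 = 7.7% |
| 50% | 1.9 | 0.050 / 0.950 = 5.3% |
| 75% | 0.9 | 0.025 / 0.925 = 2.7% |

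The table shows the direction of the error. Nothing in the Protocol fixes r or f.

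**The case against.** The case on the other side limits the point in several ways.

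- **Harm that was detected.** A reader might infer that if 3 of 30 IP patients stopped because of raised enzymes, the trial would report 0 of 27. The Protocol does not support this. With no scheduled test between day 0 and day 30, a stop for an enzyme rise presupposes an unscheduled test, so a result exists. Methods and Procedures provides for unscheduled visits, and the Study Assessment Table leaves clinical investigations to the physician. What remains is that no rule requires such results to be entered as study data.
- **Other safety data.** A reader might also infer that safety as a whole is seen only in completers. That goes too far: adverse events are recorded at every visit, and the same outcome covers the allergic symptoms. Only the scheduled laboratory part depends on day 30.
- **Stopping the IP.** Methods and Procedures and Study Treatment (c) allow the IP to be stopped after a serious event without saying that the patient leaves, so such a patient may still reach day 30. However, Study Assessments gives not taking the IP as an example of a violation that leads to withdrawal, and the passages are not reconciled.
- **Late attenders.** Patients who miss a visit window are continued in the study and can still be sampled. This does not help patients who are withdrawn.
- **The last visit.** The Study Design overview could be read as covering any final visit. The three more specific places fix the draw at day 30, so the wording at least needs aligning.
- **Role of the analysis plan.** How values are summarised can be left to the SAP, which is not shown. Whether blood is drawn at exit is part of the visit schedule and belongs in the Protocol.

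**Conclusion.** The point holds in a limited form. Patients withdrawn before day 30 have no protocol-scheduled post-baseline liver or kidney result, so change not otherwise recognised in them is lost from the laboratory safety comparison. Because some exits are for serious disease or expected harm, the loss may be informative.

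The size cannot be stated. The margins of 4 at 60 enrolled and up to 19 at 75 are spare recruitment; a reader might take the latter as a planned 25% drop-out rate, but the Protocol states none and ties no exits to harm. The conclusion rests on reading the day-30 entries as governing over the overview's looser wording. The measure is secondary and the trial exploratory, so this is an inexpensive improvement to data collection and does not invalidate the design. When treatment should be stopped is a clinical matter and is not judged here.

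**What to change.** - In Study Assessments (discontinued patients) and the Study Assessment Table, state that the liver and kidney panel planned for day 30 is drawn when a patient leaves the study early, if the patient agrees, and that the day of sampling is recorded.
- State that available unscheduled liver and kidney results are entered as study data.
- Align the overview's wording on the last visit in Study Design with this rule.
- Reconcile Methods and Procedures and Study Treatment (c) with the withdrawal rule in Study Assessments, so that it is clear whether a patient whose IP is stopped remains in the study to the day-30 sample.
- Report by arm how many patients have no post-baseline liver or kidney value. If the SAP already does this, nothing more is needed.

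**Cost.** A short amendment. For leavers it mainly moves a panel already planned for day 30 to an earlier date. Sampling times will vary among leavers, so results should be shown with the day of sampling. Patients who refuse or cannot be reached will still be missing.

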# Background and Introduction

COVID-19 (previously termed as 2019-nCoV), a novel coronavirus disease with high mortality, emerges as a pandemic disease^[[1]](#endnote-1)^. In December 2019, a series of acute atypical respiratory disease occurred in Wuhan, China. This rapidly spread from Wuhan to other areas. It was soon discovered that a novel coronavirus was responsible. The novel coronavirus was named as the severe acute respiratory syndrome coronavirus-2 (SARS-CoV-2, 2019-nCoV) due to its high homology (~80%) to SARS-CoV, which caused acute respiratory distress syndrome (ARDS) and high mortality during 2002–2003^[[2]](#endnote-2)^

The disease caused by this virus was called Coronavirus disease 19 (COVID-19) and a pandemic was declared by the World Health Organization (WHO). COVID-19 has been impacting a large number of people worldwide, being reported in more than 200 countries and territories.

SARS-CoV-2 virus primarily affects the respiratory system, although other organ systems are also involved. Lower respiratory tract infection related symptoms including fever, dry cough and dyspnea were reported in the initial case series from Wuhan, China^[[3]](#endnote-3)^. In addition, headache, dizziness, generalized weakness, vomiting and diarrhea were observed^[[4]](#endnote-4)^. It is now widely recognized that respiratory symptoms of COVID-19 are extremely heterogeneous, ranging from minimal symptoms to significant hypoxia with ARDS. In the report from Wuhan mentioned above, the time between the onset of symptoms and the development of ARDS was as short as 9 days, suggesting that the respiratory symptoms could progress rapidly. This disease could be also fatal. A growing number of patients with severe diseases have continued to succumb worldwide. Epidemiological studies have shown that mortalities are higher in elder population^[[5]](#endnote-5)^ and the incidence is much lower in children^[[6]](#endnote-6)^,^[[7]](#endnote-7)^.

Current medical management is largely supportive with no targeted therapy available. More treatment modalities are being tested in clinical trials in many countries. A large number of countries have implemented physical distancing and lockdown to mitigate further spread of the virus.

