# Subject Eligibility:

(a) Inclusion Criteria

1. Age > 18 years
2. All sexes
3. Case definitions for inclusion in the study will include mild to moderately severe cases as defined in the Guidance on appropriate treatment of suspect/confirmed case of COVI19 issued by Ministry of Health and Family Welfare, Govt of India on 07 Apr 2020.
   Mild: Cases presenting with fever and/or upper respiratory tract illness (Influenza like Illness, ILI); Moderate: Pneumonia with no signs of severe disease (Respiratory Rate 15 to 30/minute, SpO2 90%-94%). OR
4. Laboratory confirmed SARS CoV-2 infection within last 10 days or SARS CoV-2 test result pending with a high clinical suspicion as defined by: Cough of more than 10 days duration OR
5. Bilateral pulmonary infiltrates on chest X Ray / CT scan or new hypoxaemia defined as SpO2 <94% on room air, where no alternative explanation for respiratory symptoms can be given

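### The named safety outcome counts two COVID-19 symptoms as allergic reaction without a case definition, and does not name overall AE/SAE incidence by arm

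*Protocol*

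**What the plan says.** Safety is a secondary objective and part of the stated aim. The Secondary Outcomes list, which follows the adverse-event reporting format, names a safety analysis of liver and kidney function tests, "including serious allergic reaction of: rash, itching/swelling, severe dizziness, trouble breathing". The four symptoms are the only non-laboratory safety items named there.

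The Background describes COVID-19 in overlapping terms: "Lower respiratory tract infection related symptoms including fever, dry cough and dyspnea were reported" and "In addition, headache, dizziness, generalized weakness, vomiting and diarrhea were observed". Subject Eligibility admits moderate cases, meaning pneumonia with SpO2 of 90% to 94%.

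Safety data are collected more widely than the outcome suggests. At follow-up visit 1, "Questions will be asked about adherence, missed doses if any and adverse events if any", and visits 2 and 3 repeat those procedures. The Study Assessment Table ticks AE/SAE at screening, day 0, day 5, day 15 and day 30. Ethical Considerations requires SAEs to be reported within 24 hours.

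**The concern.** A patient whose pneumonia worsens and who becomes breathless has a symptom that the outcome lists as a serious allergic reaction to the capsule. Nothing in the protocol says what would make that breathlessness allergic. The number reported under this label will therefore depend partly on how COVID-19 runs in the two arms.

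Breathing also appears on the efficacy side, because restoring respiratory health is a secondary objective. A product that helped the disease would lower the allergic count for reasons unrelated to allergy, and one that worsened it would raise the count.

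Deaths, other SAEs and gastrointestinal events are collected but are not part of the named outcome. The broadest and least judgement-dependent safety comparison in the trial is therefore not the one to which the protocol commits itself.

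**Working it through.** **1. Overlap, item by item.** The outcome terms are from the Secondary Outcomes list. The disease terms are from the Background and the classification table in the Symptomatology section.

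| Outcome term | Given as a COVID-19 symptom? |
|---|---|
| Rash | No |
| Itching/swelling | No |
| Severe dizziness | Dizziness, without a severity grade |
| Trouble breathing | Dyspnoea |

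Two of four overlap. This counts terms and does not measure bias.

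**2. What the placebo arm achieves.** Let b be the background rate of an overlapping symptom, h the extra rate from hypersensitivity, and e the change that the product causes through the disease. The expected rates are b on placebo and b + h + e on product, so the difference is h + e. Randomisation removes b in expectation, and the comparison remains valid as a net effect. It does not isolate h. For example, with h = +10 points and e = −10 points, the difference is 10 − 10 = 0, although one patient in ten has had a reaction.

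**3. What the background costs in precision.** The protocol gives no sample size for safety. As a check on the formulas, its stated sample size (5% against 35%, two-sided 5%, 80% power, 1:1) was reproduced:

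- Kelsey: (1.960 + 0.842)² × 2 × 0.20 × 0.80 / 0.30² = 27.9, rounded up to 28. The protocol gives 28.
- Fleiss: [1.960 × √(2 × 0.20 × 0.80) + 0.842 × √(0.05 × 0.95 + 0.35 × 0.65)]² / 0.30² = 26.7, rounded up to 27. The protocol gives 27.

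The same pooled-variance method, without continuity correction, gives power for a safety comparison:

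power = Φ{[d√n − 1.960√(2p̄(1 − p̄))] / √(p₀(1 − p₀) + p₁(1 − p₁))},

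where p₀ is the background rate, d = p₁ − p₀ is the excess, and p̄ is the mean of p₀ and p₁. The per-arm sizes are 30 (flow chart) and 37 (75/2, rounded down). The background rates are assumptions.

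| Assumed background | Excess detectable with 80% power, n = 30 | Same, n = 37 |
|---|---|---|
| 0% | 22.4 points | 18.7 points |
| 5% | 27.8 | 24.2 |
| 10% | 30.9 | 27.3 |
| 20% | 34.3 | 30.7 |
| 30% | 35.5 | 32.0 |

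The normal approximation is optimistic at low rates. Fisher's exact test at 30 per arm shows the same direction for a 20-point excess: power is 57% at 0% background, 44% at 5%, 37% at 10%, 30% at 20% and 26% at 30%. For a 10-point excess, exact power is only 7% to 10% at any of these backgrounds, so the trial is too small to detect it with or without the overlap.

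**The case against.** **Drug harm and disease cannot be told apart.** A reader might infer this from the overlap, but the design does not support it. The trial is randomised, double-blind and 1:1, and the protocol says that placebo is used to limit bias in the safety assessment as well as the efficacy assessment. Both arms carry the disease, so a between-arm excess is interpretable. What remains is weak attribution in the individual patient, an estimate that is net of any effect on the disease, and the loss of precision shown above.

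**Events attributed to COVID-19 drop out of the outcome.** This might be inferred from the reporting format, whose event section is titled for suspected drug reactions. That format serves case reporting to the Ethics Committee. The outcome itself sets no attribution rule, and assessing staff are blinded, so knowledge of treatment should not drive any misattribution.

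**SAEs, deaths and other events are excluded from analysis.** The protocol does not say so. The word including does not clearly close the list, Data Analysis says that all collected data will be analysed, and tabulation of AEs may be set out in an SAP that is not at hand. It does stand that the outcome, as named, does not mention overall AE/SAE incidence.

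**Existing qualifiers and safeguards.** The outcome says severe dizziness and serious reaction, and the form asks for severity, a specific diagnosis where possible, and dechallenge and rechallenge information. These help with single cases. They are not a case definition, no grading of severity is given, and trouble breathing has no qualifier.

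**Conclusion.** The point holds as a matter of how the outcome is specified. The protocol labels four non-specific symptoms as serious allergic reaction. Two of them are symptoms of the disease under study, and no definition separates the two causes. Overall AE/SAE incidence by arm is not named as an outcome although the data are collected at every visit.

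The consequence is moderate. The blinded comparison stays valid as a net effect, but its label promises hypersensitivity and it measures a mixture. With assumed backgrounds of 0% to 20%, the detectable excess at 30 per arm rises by about 12 points (34.3 − 22.4 = 11.9), and at 37 per arm by the same amount (30.7 − 18.7 = 12.0). These figures rest on background rates that the protocol does not give and on no loss to follow-up. Larger enrolment, which the Methods section allows for, would reduce them without changing the direction. Safety is a secondary outcome in a trial described as exploratory, so this is an inexpensive improvement and does not threaten the trial.

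**What to change.** Reword the safety outcome as all treatment-emergent AEs and SAEs, including deaths, compared by arm regardless of attribution, plus liver and kidney function tests. Define treatment-emergent from the first capsule, because the visit table also records AEs at screening.

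Report hypersensitivity as a separate item under a case definition written for analysis. It should be workable from telephone contacts, since day 15 may be and day 30 will be by telephone. This item addresses the mixture problem, because an all-AE count of breathlessness is still a net effect. The symptom warning given to patients in the Adverse Events text stays as it is.

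Use the existing day 0 questionnaire and examination to record dyspnoea and dizziness, so that new or worsened events can be identified. The patient's own answers matter here, because the protocol allows examination findings to be extrapolated when the physician cannot examine.

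The cost is protocol wording and, at most, a few CRF fields, with no new visit or procedure. The downside is a longer AE listing that includes COVID-related events in both arms.
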